## Abstract

**Background:**

Obesity is growing at an alarming rate in Latin America. Lifestyle behaviours such as physical activity and dietary intake have been largely associated with obesity in many countries; however studies that combine nutrition and physical activity assessment in representative samples of Latin American countries are lacking. The aim of this study is to present the design rationale of the Latin American Study of Nutrition and Health/*Estudio Latinoamericano de Nutrición y Salud* (ELANS) with a particular focus on its quality control procedures and recruitment processes.

**Methods/Design:**

The ELANS is a multicenter cross-sectional nutrition and health surveillance study of a nationally representative sample of urban populations from eight Latin American countries (Argentina, Brazil, Chile, Colombia, Costa Rica, Ecuador, Perú and Venezuela). A standard study protocol was designed to evaluate the nutritional intakes, physical activity levels, and anthropometric measurements of 9000 enrolled participants. The study was based on a complex, multistage sample design and the sample was stratified by gender, age (15 to 65 years old) and socioeconomic level. A small-scale pilot study was performed in each country to test the procedures and tools.

**Discussion:**

This study will provide valuable information and a unique dataset regarding Latin America that will enable cross-country comparisons of nutritional statuses that focus on energy and macro- and micronutrient intakes, food patterns, and energy expenditure.

**Trial Registration:**

Clinical Trials NCT02226627

## Background

According to the World Health Organization, more than 1.4 billion adults were overweight and more than half a billion were obese worldwide in 2008, and the prevalence of obesity nearly doubled between 1980 and 2008 [1]. According to World Health Organization, in the Americas including the United States and non-continental countries, 61 % of adults are overweight or obese in 2014 [2]. In Latin America, nearly a quarter of the population is obese, and the prevalence has increased to a greater magnitude in Mexico, Argentina, and Chile. A recent review estimated that 20–25 % of the children and adolescents (0–18 years) of Latin American are overweight or obese [3]. Time trends suggest that these figures might rise further and by 2030 up to 81.9 % of the Latin American and the Caribbean adult population could be either overweight or obese [4].

These rapid epidemiological changes in the majority of developing countries over the last decades have occurred in the framework of the so-called nutritional transition. The concept of the nutritional transition includes a shift in dietary intake and energy expenditure both of which are influenced by ongoing interactions between economic, demographic, environmental, psychosocial and cultural factors and are occurring simultaneously in society [5]. Latin American countries are experiencing different stages of the nutrition transition, although the prevalence of undernutrition is declining at different rates, and the prevalence of overweight is dramatically increasing [6].

Eating patterns that are characterized by high energy density diets, increased intakes of processed foods containing large amounts of refined sugars and saturated fats, and low intakes of fiber and micronutrients is considered the major preventable behavioral risk factors for obesity [7–9]. Physical inactivity and sedentary behavior are also a preventable behavior associated with obesity, but the evidence on this issue remains mixed, [10], and the results might not be generalizable to all world regions [11]. Furthermore, most of the information available about the role of dietary and physical activity profiles in obesity has come from studies that have been conducted in high income, developed countries, but similar evidence from developing countries is limited. In the last decade studies started to be conducted in developing countries such as Brazil [12] and China [13]. However, there is insufficient evidence about whether the same dietary and physical activity patterns and similar associations with various sociodemographic conditions can be found in different regions of middle-income countries.

Although national surveys on nutrition already exist in some Latin American countries [14–21], the majority of the data available are based on Household Consumption and Expenditures Surveys which provide consumption data at the household level and are not accurate for calculations of individual energy intake, or representative samples of entire population in each country were not employed.

An overview of the most recent nutrition surveys conducted at individual level in nationally representative household samples of Latin America is presented in Table 1. Only a handful of countries, however, have conducted surveys with face-to-face assessment of food intake for reasons of cost, expediency and logistics [22].

**Table 1 Tab1:** Cross-sectional household nutrition surveys conducted in representative samples of Latin America

Country	Year of data collection	Sample size	Sample size that underwent dietary assessment	Method	Analysis of the dietary data	Reference
Argentina (National Survey of Nutrition and Health - ENNyS)	2004–2005	36,354 (aged 6 m - 5 y and women 10–49 y)	36,354	24-h Recall	Food Composition database developed for ENNyS	[16]
Brasil (Household Budget Survey - POF)	2008–2009	159,941 (aged ≥ 0 y)	34,003 (aged ≥ 10 y)	Two 24-h recall	NDSR software [44] and Food Composition database developed for POF [45]	[46]
Colombia (National Nutritional Situation Survey -ENSIN)	2008–2010	162,331 (aged 0–64 y)	17,897 (aged 5–64 y)	Food-Frequency Questionnaire	Qualitative (daily frequency of intake)	[18]
Chile (National Food Consumption Survey - ENCA)	2014	4920 (aged ≥2 y)	4920	Quantitative Food-Frequency Questionnaire and 24-h Recall	PC-SIDE software	[14]
Ecuador (Ecuadorian National Health and Nutrition Survey - ENSANUT-ECU)	2011–2013	57,727 (aged 0–59 y)	19,932 (aged 1–59 y)	24-h Recall	PC-SIDE software	[47]
México (National Health and Nutrition Survey - ENSANUT)	2012	96,031 (aged >0 y)	10,563 to 12,484 according to method used	Semi-quantitative Food Frequency and 24-h recall in 11 % and 13 % of sample, respectively	Food Composition database developed by National Institute of Public Health [48]	[49]
Perú (National Survey of Nutritional, Biochemical, Socioeconomic and Cultural Indicators – ENINBSC)	2006	4206 (aged ≥20 y)	4206	24-h Recall	ANDREA software [50], developed by CENAN-INS	[20]
Venezuela (Encuesta de Seguimiento al Consumo de Alimentos - ESCA)	2012-2014	20,670 (aged ≥ 3 y)	6316 participants aged ≥ 3 y	Diet history and food frequency questionnaire	Food Composition database developed for ESCA	[51]

Determinations of the dietary patterns and energy and nutrient intakes are critical for developing dietary recommendations and policies to address the adverse consequences of inappropriate dietary patterns and physical inactivity. This information would be of the greatest actionable value to governments, the food and beverage industries and agriculture.

Studies that combine nutrition and physical activity assessment in representative samples of Latin American countries are lacking. In this direction, the Latin American Study of Nutrition and Health/*Estudio Latinoamericano de Nutrición y Salud* (ELANS), which is randomized cross-sectional multicenter investigation of the nutritional and physical activity statuses of adolescents and adults in eight Latin American countries, was designed. The study aims to (1) provide up-to-date reliable and comparable data of dietary intake, physical activity, and its association with anthropometric profile among representative urban populations of eight Latin American countries; (2) measure variation in overweight, dietary intake and physical activity by region, cultural background, socioeconomic status, age and gender; (3) add new scientific-based evidence to describe the interplay among energy intake, energy expenditure, and anthropometric measurements. Our overarching hypothesis is that the relationships between dietary and physical activity profiles will differ across countries and across different environmental settings.

Up to now, there is no Latin American study using a central standard methodology across a group of participating countries. Previous multicenter studies [23–26] were important references to determine the rationale and design of ELANS.

The purpose of this report is to describe the design and methodology of the ELANS. The study is currently ending the fieldwork data collection.

### Overall design and methods

The ELANS is a household-based multi-national cross-sectional survey that was conducted over a period of one year in eight Latin American countries (i.e., Argentina, Brazil, Chile, Colombia, Costa Rica, Ecuador, Perú, and Venezuela; Fig. 1) that represent approximately 60 % of the total countries of Latin America. All of the study sites are academy (universities and other academic institutions)-based and adhered to a common study protocol for interviewer training, implementation of fieldwork, data collection and management, and quality control procedures that will be simultaneously performed.

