### Data collection instruments

The ELANS protocol includes data collected via questionnaires and objective measurements. The questionnaires were administered in 2 household visits (Fig. 2). The first visit involved the selection of a respondent within the household. Additionally, the first visit also included application of the SEL questionnaire and 24-h dietary recall (24-h), and assessment of anthropometric measurements. In the first visit, a subsample received instructions regarding the use of an accelerometer with a diary to be filled out for 7 consecutive days. The second visit was performed 8 days after the first contact for the participants who were given accelerometers and 4 days later for the participants who were not given accelerometers. The second visit also included the administration of a second 24-h, the IPAQ-Long Questionnaire, and a beverage intake questionnaire (BEVQ) and the retrieval of the accelerometer.

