#### Objectively assessed activity

To objectively monitor physical activity and inactivity, 40 % of the sample was asked to wear a triaxial accelerometer (model GT3X+, ActiGraph, Pensacola, FL, USA) on an elasticized belt at hip level on the right mid-axillary line for 7 days. The participants were asked to wear the device while they are awake and to take it off for sleeping, showering or swimming. Verbal (in person and by demonstration) and written instructions on how to wear the accelerometer were provided. To further ensure protocol compliance, participants filled in an accelerometer log indicating the start- and end-time of use per day. Following the final day of data collection, the accelerometers was returned to the study sites, and the research team verified the data for completeness using the ActiLife software version 6 (ActiGraph, Pensacola, FL). At least 5 days of recording with a minimum of 10 or more hours of registration per day including at least one weekend day were required for data inclusion and analysis. The sampling interval (epoch) was set at 30 records per second.

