### Analysis plan

The primary outcome of interest will be to describe the distributions of overweight and obesity, and energy intake and expenditure intake across the countries and regions of the study. A secondary objective of the study will be to identify the individual characteristics associated with the two main outcomes of interest (obesity and energy intake/expenditure) and to test whether these associations vary across the different regions by applying the statistical methodologies described below. These individual characteristics of interest will include, but are not be limited to, education, marital status, age, sex and individual income. The results of the three main outcomes will also be presented after stratification for each of the individual characteristics.

Initially, basic statistical models will be applied to analyze the aggregated results for all the individuals in the multicenter study to identify the individual characteristics (independent of area of residence) associated with each of the outcomes, with the inclusion of all the projected 9000 individuals. Separate individual models for each of the countries will also be performed.

We will also test the presence of statistically significant differences between regions of residence and countries by adjusting multilevel models (also known as hierarquical linear models), where the individual results will be included as the first level of the model and the region of residence as the second level of the model. Overweight and obesity will be analyzed separately as dichotomous dependent variables (vs. normal weight) by adjusting logistic multilevel models, while energy intake and expenditure will be treated as continuous dependent variables and multilevel linear models will be adjusted. We will test for a statistical difference of the dependent variables according to region of residence (a two-level model) and also by including the country of residence as the third level of the previous multilevel models. Statistical difference between the regions and the countries will be tested by analyzing the area-level variance (between-group variation) of each multilevel model.

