## Discussion

The ELANS is a comprehensive cross-sectional multicenter investigation of the nutritional and physical activity statuses of adolescents and adults in 8 Latin American countries.

An important strength of the ELANS study concerns the number of participating countries from different regions in Latin America including countries that lack data on dietary intake and physical activity level of its population. In addition, the data set allows unique comparisons of dietary and physical activity patterns, as all measurements were obtained according to standard methodology and protocols in all participating countries and all countries started the fieldwork in very near time. The objective measures of physical activity with accelerometer from subgroups of respondents, further enriches the data set. Another strength of the study is the selection and adaptation of a food composition database to make cross-country nutritional intake comparisons. Standardization at the food and nutrient levels will likely minimize systematic and random errors in nutrient intake estimations because between-country comparisons are particularly prone to error when different food composition tables are used to estimate dietary intake.

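### Recalls 4 or 8 days apart leave season inside usual intake, and no calendar term is described that would keep it out of percentiles or area comparisons

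*Protocol article*

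**What the plan says.** - **Fieldwork.** Overall design and methods calls the study a "household-based multi-national cross-sectional survey that was conducted over a period of one year in eight Latin American countries". The Sampling procedures section sets out how regions, cities, census tracts, households and respondents were chosen. It does not say when each was visited.
- **Spacing of the recalls.** Data collection instruments: "The second visit was performed 8 days after the first contact for the participants who were given accelerometers". For everyone else the gap is 4 days. The second recall is taken at that visit.
- **Activity.** The long IPAQ is given once, at the second visit. Objective data come from one 7-day wear period in a subsample: "40 % of the sample was asked to wear a triaxial accelerometer" (Objectively assessed activity).
- **Usual intake.** Dietary assessment applies the MSM to nutrients, foods and food groups and reports means and percentiles by sex. No calendar term is described.
- **Area comparison.** The models in the Analysis plan have individual, region and country levels, with an open list of individual characteristics. "Statistical difference between the regions and the countries will be tested by analyzing the area-level variance (between-group variation) of each multilevel model".
- **Comparability.** The Discussion lists among the strengths that "all countries started the fieldwork in very near time". Season is not among the listed weaknesses.

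**The concern.** The MSM separates day-to-day variation from stable differences between people by comparing a person's two recalls. Variation that hardly changes between the recalls is treated as a stable trait. Over 4 or 8 days the season hardly changes, so a person interviewed in a high-intake month looks like a habitually high consumer.

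There are two consequences, under different conditions:

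1. If interviews span the year, the distribution of usual intake is too wide, and its percentiles lie too far from the centre. Perfectly even fieldwork does not prevent this.
2. If a region or country was covered in only part of the year, its mean can carry a seasonal shift. A model with region and country levels but no date term would assign that shift to the area.

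The distribution of energy intake and expenditure across countries and regions is part of the primary outcome, so both consequences touch the main results. A near-simultaneous start does not by itself align seasons: the countries run from Chile and Argentina in the southern temperate zone to Costa Rica and Venezuela in the northern tropics.

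**Working it through.** The plan gives no figure for seasonality, so there is none to reproduce. The gaps of 4 and 8 days come from Data collection instruments. The amplitudes, the SDs and the single yearly cosine are assumptions.

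**Step 1. How much seasonal information does the pair of recalls carry?** For a yearly cosine of amplitude A and dates spread over the year, the seasonal terms d days apart correlate by cos(2πd/365.25).
- d = 4: 0.998
- d = 8: 0.991

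The within-person component therefore picks up under 1% of the seasonal variance (1 − 0.991 = 0.009 at most). With seasons of 365.25/4 = 91.3 days, only 4/91.3 = 4.4% or 8/91.3 = 8.8% of pairs cross a season boundary.

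**Step 2. Where does the seasonal variance go?** The covariance of the two recalls, which identifies the between-person variance, equals S² + (A²/2)·cos(2πd/365.25), where S is the true between-person SD. With S = 1 and A = 0.5 this is 1 + 0.125 × 0.998 = 1.125 at 4 days and 1 + 0.125 × 0.991 = 1.124 at 8 days. A simulation of 400,000 people gave 1.125 and 1.124, against a true value of 1.0.

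**Step 3. Size for percentiles.** SD inflation = √(1 + (A²/2)/S²) − 1.

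| Assumed case | A/S | Variance inflation | SD inflation |
|---|---|---|---|
| Weak season | 0.10 | 0.5% | 0.2% |
| Energy: A = 150 kcal, S = 450 kcal | 0.33 | 5.6% | 2.7% |
| Moderate season | 0.50 | 12.5% | 6.1% |
| Seasonal food: ±40% swing, 50% CV | 0.80 | 32% | 14.9% |

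For the energy case under a normal approximation, the 95th percentile moves out by 1.645 × 450 × 0.0274 ≈ 20 kcal.

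**Step 4. Size for area means.** If an area is covered evenly over a window of w months, the largest shift of its mean is A·|sin(πw/12)/(πw/12)|.

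| Window (months) | Largest shift / A | With A = 150 kcal |
|---|---|---|
| 12 | 0 | 0 |
| 9 | 0.30 | 45 kcal |
| 6 | 0.64 | 96 kcal |
| 3 | 0.90 | 135 kcal |

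These are worst cases over the position of the window. The windows actually used are not in the document.

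**The case against.** The strongest reply is that this reads silence in a condensed article as a defect. The schedule of interviews by month may well sit in the full protocol or manual of operations, the covariate list is expressly open, and a season covariate is ordinary analysis-plan detail. If every area was covered evenly for the whole year, a yearly cycle averages out of its mean and the common start date does no harm. The Discussion offers that start as one aid to comparability and does not claim that seasons match.

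Much of this stands, and it rules out several stronger readings that a reader might infer:

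- **That seasonal variation is in fact counted as country or region differences.** This needs uneven timing or a cycle that does not average out. The document does not give the timing, and its silence does not show that fieldwork was uneven.
- **That no model will carry calendar time.** It can only be said that none is described.
- **That every participant is seen within one season.** Some 4% to 9% of pairs cross a boundary, and only 40% of the sample was asked to wear the accelerometer.
- **That weight status is distorted too.** Nothing in the document shows this.
- **That a rate of false country differences can be given.** Assuming an SD of 600 kcal and the article's design effect of 1.75, Costa Rica (790) against Argentina (1200) has SE = 600 × √(1.75 × (1/790 + 1/1200)) = 36.4 kcal. A seasonal imbalance of 25, 50 or 100 kcal would then be declared a difference in 11%, 28% or 79% of surveys, against a nominal 5%. But the imbalance is assumed, and this pairwise test is not the area-variance test in the plan.

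The reply does not remove the percentile problem. That follows from the stated gaps and the stated method, and even timing over the year produces it. Nor would a date term added only to the later multilevel models repair the usual-intake distribution.

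**Conclusion.** The point holds in a limited form, as a cheap improvement. With recalls 4 or 8 days apart, the MSM cannot separate season from stable differences between people. If interviews span the year, the SD of usual intake is inflated by about 3% for energy and up to about 15% for a strongly seasonal food. Those sizes rest on the assumed amplitudes and a single yearly cosine. For energy the effect is modest; it matters more because the MSM is to be applied to individual foods and food groups.

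For area comparisons of intake and activity there is a risk, not a demonstrated bias. It is nil under even 12-month coverage with a yearly cycle, and can reach most of the seasonal amplitude for an area visited in a single quarter. The near-simultaneous start should not be relied on as evidence that seasons are aligned.

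**What to change.** All of this is analysis and reporting, assuming that visit dates were recorded.

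1. Adjust the recalls for season by country (interview month, or sine and cosine of the date) and standardise them to an even calendar year before or within the MSM. Entering season as a covariate and leaving it in each person's prediction is not enough, because that keeps the seasonal spread in the distribution.
2. Include the same country-specific term in the multilevel models for energy intake and activity.
3. Tabulate interviews by country, region and month.
4. Where a region was covered in one season only, flag its contrasts as confounded with season and do not extrapolate to the rest of the year. No model term can separate the two there.
5. Reword the Discussion so that the common start is not taken to mean seasonal comparability.

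The cost is a few extra parameters and wider intervals, most of all where coverage of the year is thin.

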**Fig. 1 Fig1:**
[figure not shown]
Latin American countries included in ELANS

### Sampling procedures

A random complex, multistage sampling of 9000 adolescents and adults aged 15.0–65.0 years, stratified by geographical location (only urban areas), gender, age and socioeconomic status was performed to select a representative sample of the urban household population of eight Latin American countries. Only urban areas were included in order to keep homogeneous population in the research, and based on the fact that almost all countries have at least 80–90 % of their population living in urban areas. Individual quotas were defined for each of these variables, which allow the identification of the total numbers of interviews required to properly represent the socio-demographic distribution under study. The survey was designed in order that no more than one subject were selected from a household.

The sampling size was calculated with a confidence level of 95 % and a maximum error of 3.49 %. A survey design effect of 1.75 was estimated based on guidance from the U.S. National Center for Health Statistics [27], and calculations of the minimum sample sizes required per strata (i.e., socioeconomic level (SEL), age, and gender) were performed for each country. Table 2 shows a detailed description of the case numbers required per strata in each of the 8 study sites.

**Table 2 Tab2:** Estimated distributions of country-specific samples according to age range, gender, and SEL

	Age range				Gender		SEL			Total sample size	Margin of error (%)
	15–19.9 years	20–34.9 years	35–49.9 years	50–65 years	Male	Female	High	Middle	Low		
Argentina	144	444	336	276	576	624	72	504	624	1200	2.83
Brazil	220	760	600	400	940	1060	520	940	540	2000	2.19
Chile	113	305	270	183	426	444	61	348	461	870	3.32
Colombia	148	443	357	283	615	615	62	357	812	1230	2.79
Costa Rica	111	300	229	150	395	395	87	450	253	790	3.49
Ecuador	128	312	224	136	400	400	104	576	120	800	3.46
Peru	165	440	308	187	528	572	209	374	517	1100	2.95
Venezuela	143	418	319	220	528	572	55	154	891	1100	2.95

The demographic data were obtained from the appropriate national statistics institutes of each country. The selection of the households was design in four stages. In the first stage, total urban population was employed to define main regions proportionally in each country first, and then select cities representing each region - main cities and other cities representatives of the region, mixing a random method and sampling criteria, and trying to fulfill urban population coverage to the maximum possible. This mixed criterion enabled an increase in the efficiency of the fieldwork according to the study characteristics. In the second stage, sampling points (census tracts) of each city were randomly selected. In the third stage, a cluster of households was selected from each sampling unit. Addresses were chosen systematically using standard random route procedures, beginning with an initial address selected at random and selection of households with three systematic jumps, that is, the selection of a given household was made by randomly picking the first home and subsequently skipping 3 households. Finally, in the fourth stage, selection of respondent within a household was performed using two criteria: in each sampling unit, half of the households the participant was selected by the next birthday criteria; in the other half selection was by quotas of gender, age, and SEL.

The field interviewer arrived at the home, show an official identification badge, a letter introducing ELANs study, and briefly explain the survey’s purpose. A screener questionnaire to enumerate the household and to determine eligibility to participate further in ELANS was fulfilled. Thereafter, the selected participant signed the informed consent form.

A telephone number was available for the participants in order to answer any questions about the research, and use of the accelerometer device.

In the following circumstances - unsuccessful attempts to contact the target individual, total refusal to participate, obstruction by a family member, or inability to participate for a specified reason (e.g., travel, agenda, hospitalization) - substitutes were chosen in the home next door, following the same random selection criteria described above.

As exclusion criteria were considered pregnant and lactating women (in the first 6 months postpartum), individuals with major physical or mental impairments that affect food intake and physical activity (e.g., musculoskeletal disease, recent surgery, severe asthma, dementia, major depression), individuals below 15 or over 65 years old, adolescents without assent and consent of a parent or legal guardian, individuals living in any residential setting other than a household (e.g., hospitals, regiments, and nursing homes), and individuals unable to read.

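### The 3.49 % maximum error and all eight country margins in Table 2 match simple random sampling and leave out the plan's own design effect of 1.75

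*Protocol article*

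**What the plan says.** The sample-size justification is in the protocol article, Sampling procedures, with Table 2.

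- Target: "The sampling size was calculated with a confidence level of 95 % and a maximum error of 3.49" %.
- Design effect, in the next sentence: "A survey design effect of 1.75 was estimated based on guidance from the U.S. National Center for Health Statistics".
- Strata: that same sentence refers to "calculations of the minimum sample sizes required per strata", meaning socioeconomic level (SEL), age and gender within each country.
- Table 2 lists each country's stratum counts, its total, and a column headed "Margin of error" (%). The margins run from 2.19 (Brazil, n = 2000) to 3.49 (Costa Rica, n = 790).
- The design is clustered. Cities are chosen first and census tracts within them, and then: "In the third stage, a cluster of households was selected from each sampling unit".

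The article does not give the proportion at which the margins were calculated, and does not say whether they include the design effect.

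**The concern.** The target error and the design effect stand in consecutive sentences as parts of one calculation. A reader will therefore take 3.49 %, and the margins in Table 2, as the precision expected from this clustered survey. If the margins were worked out as for a simple random sample, the only precision figures in the article are too favourable on the plan's own assumption.

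Country-level precision matters here because the Analysis plan makes the distribution of overweight, obesity, energy intake and expenditure across countries and regions the primary outcome. Someone using Table 2 to judge what difference between two countries could be resolved would expect a finer resolution than the design gives.

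**Working it through.** **Inputs.** From Sampling procedures and Table 2: 95 % confidence (z = 1.96), design effect 1.75, and the country totals and margins. Assumed: proportion p = 0.5, where the margin is largest.

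**Step 1: reproduce the printed margins.** Without a design effect, margin = 1.96 × √(0.25/n) = 0.98/√n. For Costa Rica, 0.98/√790 = 0.0349, or 3.49 %. The third column below agrees with the printed column to two decimals in all eight countries.

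**Step 2: include the design effect.** Multiply each margin by √1.75 = 1.323.

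| Country | n | No design effect (%) | Printed (%) | Design effect 1.75 (%) |
|---|---|---|---|---|
| Argentina | 1200 | 2.83 | 2.83 | 3.74 |
| Brazil | 2000 | 2.19 | 2.19 | 2.90 |
| Chile | 870 | 3.32 | 3.32 | 4.40 |
| Colombia | 1230 | 2.79 | 2.79 | 3.70 |
| Costa Rica | 790 | 3.49 | 3.49 | 4.61 |
| Ecuador | 800 | 3.46 | 3.46 | 4.58 |
| Peru | 1100 | 2.95 | 2.95 | 3.91 |
| Venezuela | 1100 | 2.95 | 2.95 | 3.91 |

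Solving instead for the design effect implied by each printed margin, (margin)² × n / (1.96² × 0.25), gives 0.997 to 1.002. The adjusted margins are 32 % wider than those printed. Equivalently, the printed ones are 1 − 1/1.323 = 24 % too small.

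**Step 3: size needed for 3.49 %.**
- Without a design effect: n = 1.96² × 0.25 / 0.0349² = 788, in line with Costa Rica's 790.
- With it: 1.75 × 788.5 = about 1,380. Only Brazil (2000) exceeds this.
- Costa Rica's effective size is 790/1.75 = 451.

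**Step 4: could other inputs reconcile the two figures?**
- *90 % confidence with design effect 1.75:* Costa Rica's margin is 3.87 %, not 3.49 %.
- *A different p with design effect 1.75:* p(1 − p) would have to equal 0.25/1.75 = 0.143, so p of about 0.17. The article states no such value. Using prevalences from its Background, Costa Rica's margin with the design effect is 4.50 % at p = 0.61 (overweight or obese in the Americas) and 3.99 % at p = 0.25 (roughly the obesity figure for Latin America). Both exceed 3.49 %.

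**Step 5: was the design effect used for the strata?** The cells checked are whole-percent shares of the country total:
- Argentina, age: 144, 444, 336 and 276 of 1200 = 12, 37, 28 and 23 %.
- Peru, SEL: 209, 374 and 517 of 1100 = 19, 34 and 47 %.
- Ecuador, SEL: 104, 576 and 120 of 800 = 13, 72 and 15 %.
- Venezuela, SEL: 55, 154 and 891 of 1100 = 5, 14 and 81 %.

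These look like population shares; no precision target or design effect is visible in them. For scale, the 55 people in Venezuela's high SEL group give a margin of 0.98/√55 = 13.2 %, or 17.5 % with the design effect.

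**Step 6: effect on a country comparison.** For a difference in proportions between Costa Rica and Ecuador at p = 0.5, the 95 % margin is √(3.49² + 3.46²) = 4.9 points from the printed figures and √(4.61² + 4.58²) = 6.5 points from the adjusted ones.

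**The case against.** The strongest defence is textual. The article never says outright that 3.49 % includes the design effect. The 1.75 stands in the sentence about stratum sizes, and the heading of the margin column claims no adjustment. A reader might infer that the plan expressly sized each country for 3.49 % with a design effect of 1.75; the text does not go that far. This limits the wording of the point but does not remove it. The article states a design effect, prints margins without it, and does not say that they exclude it. The stratum counts show no use of it either.

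Second, p is not stated, and p of about 0.17 would reconcile the figures. That possibility should be declared, but it sits badly with the phrase "a maximum error of 3.49" %, since a margin is at its maximum at p = 0.5.

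Third, planning margins enter no estimate. The Analysis plan specifies multilevel models with region and country levels, and clustered standard errors for the structural equation models. This stands as a limit on the consequence. It is only partial mitigation, because those levels do not include census tracts and the article does not extend them to every descriptive table.

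Fourth, 4.61 % is itself nominal. Cities were chosen partly by criteria, and respondents in half the households by quota, so no margin formula describes this sample exactly. That is also true, and it applies equally to the printed figures.

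**Conclusion.** The point holds as a wrong stated precision. The 3.49 % maximum and all eight Table 2 margins are simple-random-sampling values. On the plan's own design effect, with p = 0.5 assumed, the maximum is 4.61 % and the country margins run from 2.90 % to 4.61 %. The value 1.75 is taken from the article as it stands and was not checked against its source.

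Three stronger readings are not supported:

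- *The sample is too small or the analyses are invalid.* The article names no objective that fails at 4.61 %, and the margins play no part in the models.
- *Sparse SEL strata must be merged.* The article promises no precision by country and SEL and gives no threshold for merging.
- *Table 2 carries a wrong overall total.* The country totals add to 9,090, but the table has no overall-total row. The 9000 is in running text, is called projected in the Analysis plan, and differs by 1 %.

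A minor and separate inconsistency is that Brazil's age cells add to 220 + 760 + 600 + 400 = 1,980 against a total of 2,000. The shares 11, 38, 30 and 20 % add to 99 %, so rounded percentages may explain it.

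**What to change.** In Sampling procedures, restate the maximum error as 4.61 % at 95 % confidence, and name p = 0.5 and design effect 1.75 as its basis. Replace the Table 2 margin column with 3.74 (Argentina), 2.90 (Brazil), 4.40 (Chile), 3.70 (Colombia), 4.61 (Costa Rica), 4.58 (Ecuador), 3.91 (Peru) and 3.91 (Venezuela). Describe the stratum counts as quotas proportional to the population rather than as minimum sizes required. If a proportion other than 0.5 was in fact used, state it and recalculate the column on that basis.

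The cost is a few words and one table column. No participants are added, so the change remains possible with fieldwork ending. The only downside is a less favourable stated precision.
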